## 9. TRIAL TREATMENT

Full details relating to chemotherapy treatment duration, dose schedules, administration and modifications, interactions with other therapies and concomitant medications can be found in Appendix 2. Expected adverse events associated with CAPOX and FOLFOX regimes are included in Appendix 1. The expected protocols for long course radiotherapy can be found in Appendix 3.

### 9.1 TREATMENT DURING CHEMORADIOOTHERAPY

The planned choice of chemotherapy treatment during CRT is at the discretion of the local oncology team. Although no treatments are under evaluation during the registration period, details relating to the CRT should be recorded in the **CHEMORADIOOTHERAPY Form** once the patient completes CRT.

## 9.2 TRIAL INVESTIGATIONAL MEDICINAL PRODUCTS

The choice of systemic chemotherapy (CAPOX, FOLFOX or single agent capecitabine or 5-FU) is a stratification variable for randomisation and therefore the chemotherapy regimen to be used should be made upfront prior to patient registration according to patient choice or local practice.

For the purpose of this trial all drugs associated with the CAPOX and FOLFOX chemotherapy regimens, listed below, are considered IMPS:

- Oxaliplatin
- Capecitabine
- Fluorouracil (5-FU)
- Folinic acid (given in combination with Oxaliplatin and 5-FU in the FOLFOX regime)

Trial sites can use any brand of the IMPs listed above according to local practice.

## 9.3 DISPENSING AND DRUG SUPPLIES

A TRIGGER Trial pharmacy pack including details relating to the IMPs used in this trial will be sent to participating sites prior to site initiation. All trial drugs used in this trial are commercially available and each site will use their normally available generic hospital stock and their handling and management should be subject to standard local pharmacy procedures. Each trial site pharmacy will be responsible for drug accountability and destruction at their site as detailed in the TRIGGER pharmacy pack. All sites will ensure that all stock used will be of suitable quality as per EU GMP and only use stock that has a UK or EU marketing authorisation.

## 9.4 SUMMARY OF PRODUCT CHARACTERISTICS

The reference document relating to each of the IMPs listed in section 9.2 is the SmPC. Section 4.8 (Undesirable effects) of the SmPC represents the reference safety information for each of the IMPs, which should be used by investigators as a reference point when assessing causality and expectedness.

| Investigational medicinal product                        | Brand      |
|----------------------------------------------------------|------------|
| Capecitabine 150mg film coated tablet                    | Accord     |
| Capecitabine 500mg Film coated tablet                    | Accord     |
| Fluorouracil 25mg/ml Injection                           | Hospira UK |
| Fluorouracil 50mg/ml Injection                           | Hospira UK |
| Oxaliplatin 5mg/ml Concentrate for Solution for Infusion | Hospira UK |
| Calcium folinate 10mg/ml Injection                       | Hospira UK |

## 10. ASSESSMENT SCHEDULES

Please refer to the assessment schedules below for details of assessments to be performed, timelines and the CRFs to complete (further details relating to CRF completion can be found at the front of the CRF pack).

- Radiological assessment will be performed as per [Appendix 6](#) with synoptic reporting according to the allocated **POST-TREATMENT MRI FORM**.
- Chemotherapy toxicity will be assessed at the end of each cycle during treatment and residual toxicity assessed at the 12-month follow-up visit.
- When surgery is performed, surgical morbidity will be recorded intra-operatively and both early (6 weeks) and late (up to 12 months) surgical complications will be recorded post-operatively.
- **The QUALITY OF LIFE Form** will be completed by all patients at registration. For patients that undergo surgery the QoL forms should be completed again at 1 and 3 years following the completion of CRT. For patients who defer surgery the QoL forms should be completed at 1, 3 and 5 years from the time of CRT completion.
- Adverse events should be recorded from the date of the post-CRT MRI scan until 30 days after the patient's last dose of chemotherapy received during the intervention phase of the trial. Residual toxicity will be assessed at 12 months. Concurrent medications should be recorded at registration and updated from randomization until 30 days after the patient's last dose of chemotherapy. .
- **ANNUAL FOLLOW-UP Forms** should be completed at 12 months from the end of CRT and annually thereafter up to 3 years in those that undergo surgery and up to 5 years in those who defer surgery.

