## **8.1 THE CONTROL ARM – BEST CURRENT PRACTICE**

1. **Post-CRT restaging** – The post-CRT MRI must be **performed within 4-6 weeks (no later than 10 weeks)** from completion of CRT.
2. The radiologist will be notified that the patient has been randomised into the control arm. Radiologist completes the **CONTROL ARM POST-TREATMENT MRI Form**.
3. **Surgery** is planned according to the baseline MRI and should be performed 6-12 weeks after CRT completion. A prepared **SURGERY Form** should be enclosed in the patient notes so that the surgeon can complete the form immediately after surgery.
4. A routine surgical follow up appointment will occur 4-6 weeks after surgery, therefore the **SURGICAL MORBIDITY** and **PATHOLOGY REPORTING Forms** should be completed at 6 weeks. These forms may be completed retrospectively up to 12 weeks after surgery but only complications that occur within the first 6 weeks should be recorded on the **SURGICAL MORBIDITY Form**.
5. **Adjuvant Chemotherapy** - Please complete the **CHEMOTHERAPY and TOXICITY Forms** at the end of each cycle i.e. at the end of each 3-weekly cycle of CAPOX (or single agent capecitabine) or at the end of each 2-weekly cycle of FOLFOX (or single agent 5-FU).
6. **Oncological outcomes** – 12 months from the completion of CRT please complete the **ANNUAL FOLLOW-UP Form**, and further **SURGICAL MORBIDITY** and **TOXICITY Forms** to capture late surgical complications and residual toxicity respectively. To avoid the inevitable distress caused by the relative of a dead patient receiving questionnaires, please ensure this is completed in parallel with the follow-up for Patient Reported Outcome Measures (PROMs).
7. **PROMs** – 12 months from the completion of CRT, the recruiting trial site will need to invite the patient to complete a postal questionnaire (**QUALITY OF LIFE forms**) that includes 40 questions about symptoms and quality of life. The patient will have completed the questionnaires at entry into the study and will be expecting to receive the forms. A freepost envelope addressed to the recruiting trial site will also be provided. If the patient does not initially respond please contact them by phone – to

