## **8.2 INTERVENTION ARM – A ‘GOOD RESPONSE’ TO CHEMORADIOOTHERAPY (MRTRG 1 & 2)**

1. **Post-CRT restaging** – The post-CRT MRI must be **performed within 4-6 (no later than 10) weeks** of completing CRT. Ensure the Radiologist receives the appropriate reporting form – **INTERVENTION ARM POST-TREATMENT MRI Form** which includes the mrTRG datafields.
2. Radiologist completes the INTERVENTION ARM POST-TREATMENT MRI Form – **mrTRG 1 or 2 reported mrTRG directed management results in the patient being offered deferral of surgery.**
3. The option of deferral of surgery is discussed with the patient, and intensive active monitoring is undertaken. **Please refer to the 5 year surveillance schedule in Section 11.2 Deferral of Surgery Follow-up.** The **INTERVENTION ARM POST-TREATMENT MRI Form** should be completed each time an MRI scan is performed during the surveillance period.
4. **Chemotherapy** (Appendix 2) – The patient will receive 24 weeks of chemotherapy (8 cycles of CAPOX or 12 cycles of FOLFOX) and this should start within 12 weeks of CRT completion. Please complete the **CHEMOTHERAPY AND TOXICITY Forms** at the end of each cycle i.e. at the end of each 3-weekly cycle of CAPOX (or single agent capecitabine) or at the end of each 2-weekly cycle of FOLFOX (or single agent 5-FU).
5. **Mid-chemotherapy MRI scan** – an MRI scan should be performed approximately mid-way through chemotherapy treatment once the patient has received 12 weeks of treatment. The **INTERVENTION ARM POST-TREATMENT MRI Form** should be completed.
6. **Oncological outcomes**– 12 months from the completion of CRT please complete the **ANNUAL FOLLOW-UP Form**, and a further **TOXICITY Form** to assess residual toxicity. To avoid the inevitable distress caused by the relative of a dead patient receiving questionnaires, please ensure this is completed in parallel with the follow-up for Patient Reported Outcome Measures (PROMs).
7. **PROMs** -12 months from the end of CRT, the recruiting trial site will need to invite the patient to complete a postal questionnaire (**QUALITY OF LIFE Form**) that includes 40 questions about symptoms and quality of life. The patient will have completed the questionnaire at entry into the study and will

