### 8.3 EXPERIMENTAL ARM – A ‘POOR RESPONSE’ TO CHEMORADIOOTHERAPY

1. **Post-CRT restaging** – The post-CRT MRI must be performed within 4-6 (no later than 10) weeks of completing CRT.
2. Radiologist completes the **INTERVENTION ARM POST-TREATMENT MRI Form – mrTRG 3 –5 reported.**
3. **mrTRG directed management results in the patient being offered additional chemotherapy before a decision is made regarding surgery.**
4. The option of **additional pre-operative chemotherapy** is discussed with the patient. **Chemotherapy** (Appendix 2) – The patient will receive 12 weeks (4 cycles of CAPOX or 6 cycles of FOLFOX); this should start within 12 weeks of CRT completion. Please complete the **CHEMOTHERAPY** and **TOXICITY Forms** at the end of each cycle i.e. at the end of each 3-weekly cycle of CAPOX (or single agent capecitabine) or at the end of each 2-weekly cycle of FOLFOX (or single agent 5-FU).
5. Following the completion of 12 weeks of chemotherapy a repeat MRI should be performed 4-6 weeks later and mrTRG reported. Ensure the Radiologist receives the appropriate reporting form – **INTERVENTION ARM POST-TREATMENT MRI Form** which includes the mrTRG data fields. The Radiologist completes the **INTERVENTION ARM POST-TREATMENT MRI Form**.

**mrTRG directed management results in the patient being offered deferral of surgery (if mrTRG improved to I or II) or proceeding to surgery (mrTRG remains III-V). The options of surgery or deferral of surgery as appropriate should be discussed with the patient.**

- If mrTRG now I or II and it is agreed that patient should defer surgery then patients should receive the remaining 12 weeks of chemotherapy as soon as possible following the repeat MRI and MDT meeting and be followed up in the same way as those in the ‘good-response’ sub-group described above and undergo the 5 year surveillance schedule detailed in Section 11.2.1.

- If mrTRG remains III-V then patient proceeds to surgery and undergoes the following:

6. **Surgery** is planned according to the baseline and post-treatment MRI and should be performed **6-12 weeks after pre-operative chemotherapy** is completed. A prepared **SURGERY Form** should be enclosed in the patient notes so that the surgeon can complete the form immediately after surgery.

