7. A routine surgical follow up appointment will occur 4-6 weeks after surgery, therefore the **SURGICAL MORBIDITY** and **PATHOLOGY REPORTING Forms** will be completed at 6 weeks. The **SURGICAL MORBIDITY Form** may be completed retrospectively up to 12 weeks after surgery but only complications that occur within the first 6 weeks should be recorded.

8. **Adjuvant Chemotherapy** - The patient will receive 12 weeks (4 cycles of CAPOX or 6 cycles of FOLFOX). Please complete the **CHEMOTHERAPY** and **TOXICITY Forms** at the end of each cycle i.e. at the end of each 3-weekly cycle of CAPOX (or single agent capecitabine) or at the end of each 2-weekly cycle of FOLFOX (or single agent 5-FU).
9. Oncological outcomes – 12 months from the end of CRT please complete the ANNUAL FOLLOW-UP Form, and a further **SURGICAL MORBIDITY** and **TOXICITY Forms** to capture late surgical complications and residual toxicity respectively. To avoid the inevitable distress caused by the relative of a dead patient receiving questionnaires, please ensure this is completed in parallel with the follow-up for Patient Reported Outcome Measures (PROMs).
10. **PROMs** -12 months from the end of CRT, the recruiting trial site will need to invite the patient to complete a postal questionnaire (**QUALITY OF LIFE Form**) that includes 40 questions about symptoms and quality of life. The patient will have completed the questionnaire at entry into the study and will be expecting to receive the forms. A freepost envelope addressed to the recruiting trial site will also be provided. If the patient does not initially respond please contact them by phone – to confirm the questionnaires arrived and to re-send if necessary. If there is no response send a second questionnaire at 2 weeks later. If there is no response by 12 weeks (15 months from the end of CRT), we will accept that the patient preferred not to take part. If the patient has a disability that prohibits them from completing the forms by hand we recommend reading the questions out over the phone.
11. **Oncological outcomes** – 24 months and 36 months following the end of CRT please complete the **ANNUAL FOLLOW-UP Form**.
12. **PROMs** - 36 months (not at 24 months) following the end of CRT the patients will be asked to complete the same **QUALITY OF LIFE form**.

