b if patient has consented to additional blood sample collection for research.

- c The post-CRT MRI should to be performed within 4-6 weeks (maximum of 10 weeks) from completion of CRT.
- d Both early (4-6 weeks) and late surgical complications (at 12 months) will be recorded.
- e Resected specimen will be prepared and evaluated using a standardized method described in Appendix 5.
- f All adverse events will be recorded from the date the Post-CRT MRI scan is performed until 30 days after the last dose of chemotherapy is administered during the Intervention Phase of the trial.
- g Disease status at 5 years (does not require clinic visit): alive without metastatic or recurrent disease, alive with metastatic and/or recurrent disease (date diagnosed), dead (date of death)
- h Patient consent to randomisation can take place at any time during CRT or once CRT is complete but at least 1 week prior to the post-CRT MRI scan

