## **2 REPORTING PROCEDURES FOR ALL ADVERSE EVENTS**

The investigator is responsible for ensuring that all adverse events (including SAEs) observed by the investigator or reported by patients from the date of the post-CRT MRI scan is performed until 30 days after the last dose of chemotherapy is administered are properly captured in the patients' medical records (source documents). Adverse events occurring in all arms of the trial should be reported with the same diligence so that bias is not introduced to the apparent incidence of adverse events observed in the intervention arm. In addition, the investigator is responsible for ensuring that, for those patients randomised, all adverse events captured on the patients' medical records (as specified above) are reported on the CRF.

**NOTE: The rationale for commencing AE recording from the date of the post-CRT MRI rather than the date of randomization is to avoid capturing AEs during and shortly after the last two weeks of CRT i.e. those that could be possibly related to CRT rather than the IMP(s) (systemic chemotherapy) received as part of the trial, which patients do not receive until after the post-CRT MRI scan is performed 4-6 weeks after the completion of CRT.**

As per assessment schedules residual toxicity will be assessed at the 12 month clinic visit.

In the TRIGGER trial, the seriousness, causality and expectedness of all adverse events will be assessed by the principal investigator (or delegate) at the participating site. Upon receipt at the trial management centre, all SAEs will be also reviewed by the Chief Investigator and CTIMP Lead at the Royal Marsden (or delegate).

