## 1.1 CHEMOTHERAPY TREATMENT POST-SURGERY

Adjuvant chemotherapy should commence 4-12 weeks (ideally 6-8 weeks) after surgery. If this is delayed beyond 12 weeks, for example due to post-operative complications, the patient must be discussed with the lead centre (RMH) in order to determine if proceeding with adjuvant treatment is still appropriate.

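### The single scheduled residual-toxicity form is timed from the end of CRT, so time since last dose differs by pathway and some operated poor responders may still be on treatment

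*Protocol*

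**What the plan says.** Section 10 sets two kinds of toxicity reading: "Chemotherapy toxicity will be assessed at the end of each cycle during treatment and residual toxicity assessed at the 12-month follow-up visit". Appendix 1, Section 2, repeats the second: "As per assessment schedules residual toxicity will be assessed at the 12 month clinic visit". The 12-month clock starts at the end of CRT in every pathway. Section 8.1 has "12 months from the completion of CRT please complete the" follow-up forms, and Sections 8.2, 8.3 and 11.2.1 use the same anchor. In the poor-response pathway (Section 8.3) the 12-month surgical morbidity and toxicity forms are there "to capture late surgical complications and residual toxicity respectively". No pathway schedules a later toxicity form, and none ties one to the last dose.

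Appendix 2 gives every pathway the same planned total of chemotherapy and varies only when it is given. Control patients receive all of it after surgery, good responders during deferral, and operated poor responders half before and half after surgery.

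**The concern.** A residual-toxicity form is meant to show what remains once treatment is over. For that reading to mean the same thing in each group, patients should have had roughly similar recovery time. Here the form is fixed on a clock that ignores when chemotherapy ended, while the pathways are built to end chemotherapy at different times. Good responders then have the longest recovery and operated poor responders the shortest. Timing alone could make lasting toxicity look milder in the first group and worse in the second. A patient treated entirely within the permitted windows could also complete a form labelled residual while still receiving cycles.

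This matters because the feasibility stage is meant to inform the safety and acceptability of extra pre-operative chemotherapy (Sections 4 and 14.1.2), and its patients are to enter the phase III analysis (Section 3.1).

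**Working it through.** The Protocol states no figure for this gap, so there is nothing to reproduce. The check adds up its own windows, in weeks from the end of CRT, and takes the 12-month visit as week 52.

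**Inputs**
- Restaging MRI, Section 10.1 notes: "The post-CRT MRI should to be performed within 4-6 weeks (maximum of 10 weeks) from completion of CRT". The earliest intervention-arm chemotherapy start is therefore taken as week 4. This is an assumption, because the Protocol gives only the latest start.
- Latest intervention-arm start, Section 8.2, with the same limit in 8.3: "this should start within 12 weeks of CRT completion".
- Control surgery: weeks 6 to 12 (Section 8.1).
- Surgery in poor responders, Section 8.3: "6-12 weeks after pre-operative chemotherapy".
- Post-operative start, Appendix 2, Section 1.1: "Adjuvant chemotherapy should commence 4-12 weeks (ideally 6-8 weeks) after surgery".
- Chemotherapy duration: 24 weeks in control and good responders; 12 + 12 weeks in poor responders.
- Poor responders who convert to deferral: repeat MRI 4 to 6 weeks after the first 12 weeks, then the remaining 12 weeks as soon as possible (Section 8.3).

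**Formula:** gap = 52 − week in which the last planned cycle ends.

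| Pathway | End of chemotherapy (weeks) | Gap to 12-month form (weeks) |
|---|---|---|
| Control | (6 to 12) + (4 to 12) + 24 = 34 to 48 | 4 to 18 |
| Good responders | (4 to 12) + 24 = 28 to 36 | 16 to 24 |
| Poor responders converting to deferral | (4 to 12) + 12 + (4 to 6) + 12 = 32 to 42 | 10 to 20 |
| Operated poor responders | (4 to 12) + 12 + (6 to 12) + (4 to 12) + 12 = 38 to 60 | −8 to 14 |

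A negative gap means the form is due before planned treatment ends. The midpoints are 11, 20, 15 and 3 weeks.

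**Sensitivity**
- The week-4 assumption affects only the longest gaps in the three intervention rows. With a week-6 start the operated poor-responder range becomes −8 to 12. The −8 uses only stated upper limits.
- With the preferred 6 to 8 week post-operative start, control is 8 to 16 and operated poor responders are −4 to 12.
- Section 11.2.1 allows ±1 month (about 4.3 weeks) at the 1-year deferral visit. Good responders then range from 52 − 4.3 − 36 = 11.7 to 52 + 4.3 − 28 = 28.3, about 12 to 28 weeks.
- Appendix 2, Section 6.1, allows a toxicity delay of up to 3 weeks. One such delay takes the control minimum to 4 − 3 = 1 and the operated poor-responder minimum to −8 − 3 = −11.

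**How often the form falls on treatment.** The Protocol gives no distribution within its windows. If each is taken as uniform and independent, purely for illustration, about 22% of operated poor responders would still be on treatment at week 52, or about 10% with the 6 to 8 week post-operative start.

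**At 24 months (week 104):** the smallest gap is 104 − 60 = 44 weeks, or 104 − 63 = 41 with one 3-week delay.

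**The case against.** The strongest reply is that no planned comparison depends on this form. The listed toxicity endpoint is acute grade 3-5 toxicity (Sections 4.4.2 and 14.2.2), which the per-cycle forms supply. Residual toxicity is not a listed endpoint, and Section 14.2.2 rules out formal comparisons for unlisted ones. That stands. A reader might infer that the trial's toxicity comparison is biased, but the documents do not support this; only a descriptive reading of the 12-month form is affected.

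A reader might also take this form to be the only information on lasting toxicity. It is not. Adverse events are recorded until 30 days after the last dose, and Appendix 1, Section 2.4, has drug-related events followed until they clear, return to baseline or settle. What is single is the scheduled, systematic reading.

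A third tempting inference is that poor responders in general are still on treatment at 12 months. Those who convert to deferral are not, under the planned windows. Among those operated on, it takes several intervals near their upper limits together.

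Finally, a common clock from the end of CRT is defensible in a comparison of strategies: it shows the patient's state at one year under each. That is a fair reason to keep the 12-month form. It does not make the form a measure of residual toxicity in someone still receiving cycles, and it does not remove the need to know time since last dose when reading it. The analysis plan, which is not shown, may deal with the reporting, but the absence of a later scheduled form is fixed by the Protocol.

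**Conclusion.** The point holds as a limited weakness of measurement timing. At the one scheduled residual reading, recovery time differs systematically by pathway: 4 to 18 weeks in control, 16 to 24 in good responders, 10 to 20 in poor responders who convert to deferral, and −8 to 14 in operated poor responders. Pathway is therefore confounded with time since last dose. In the late part of the operated poor-responder windows, a compliant patient would complete the form during adjuvant chemotherapy.

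The ranges rest on a week-4 earliest start in the intervention arm, no cycle delays, completion of the planned cycles and a visit at week 52. The primary recruitment endpoint and the acute grade 3-5 toxicity endpoint are untouched. This is an improvement worth making, not a flaw that threatens the trial's conclusions.

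**What to change.** - Keep the 12-month TOXICITY form as it is.
- Repeat the same form at the 24-month annual follow-up, which Sections 8.1, 8.2 and 8.3 already schedule in every pathway. It falls about 44 weeks or more after the last planned cycle, or about 41 with one 3-week delay.
- Report the 12-month form for all patients by weeks since last dose. This presumes that the CHEMOTHERAPY form, completed each cycle, carries the dates.
- Flag forms completed on treatment or within 30 days of a dose, but do not exclude them. Exclusion would be a post-randomisation selection falling almost entirely on operated poor responders.

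The cost is one extra form per patient at an existing visit, with the matching change to the assessment schedules. The reporting change needs no new data if the dose dates are recorded. Nothing here alters the timing or content of treatment.
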